### Assessments

The main aim of the current study is to assess the efficacy of the intervention in the general population and an ASD population, but also if people with high levels of alexithymia gain additional benefit. Further, this study will aim to replicate the study by Cook et al [32], which suggested that alexithymia, not ASD, predicts poor FEER. This requires having a general population group and another group with people with ASD, with both groups being matched on levels of alexithymia. Therefore, participants will be prescreened online to facilitate creating this composition of participants. During the online screening stage, participants will choose to consent in the study, complete the TAS-20, and indicate if they have an ASD or if they have been diagnosed with an ASD. During this screening stage, participants will also complete demographic information, the Autism Spectrum Quotient (AQ-10) [42], and the K-10.

Participants will then be invited to a clinical interview with a provisional psychologist (PP) at the Federation University Psychology Clinic who will confirm a reported diagnosis of ASD and complete an observational assessment that gives a diagnostic indication of an ASD. Participants who have reported a diagnosis will be asked what instrument was used and if the PP can request a copy of the results. The PP will also complete the Autism Mental Status Exam 2.2 (AMSE) [43,44]. The AMSE is an 8-item observational assessment that takes place during a clinical interview and predicts ASD classification on the Autism Diagnostic Observation Schedule (ADOS) [45]. During this clinical interview, participants will also be administered the Depression Anxiety Stress Scales-21 (DASS-21) [46] and the Wechsler Abbreviated Scale of Intelligence (WASI-II) [47] to assess depression, anxiety, and IQ, which will be used as control variables in the analyses of the results.

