## Introduction

### Background

Behavioral and cognitive neuroscience has elaborated a range of emotion-related difficulties with emotion recognition [1], empathy [2], and regulation of emotions in autism spectrum disorder (ASD) [3]. However, these abnormalities are not observed in all people with ASD [4]. Traditionally, these emotion-processing difficulties have been viewed as inevitable correlates of ASD, but recent research suggests that their presence is variable and better explained by co-occurring alexithymia. This suggestion is termed the alexithymia hypothesis [5] and is gaining significant support [6]. Alexithymia is a personality construct that relates to the inability to distinguish or describe the subjective feelings in the body produced by emotion. Alexithymia is related to both empathy [7] and emotion recognition [8] deficits. Severe degrees of alexithymia are manifested in up to 65% of adults with ASD [9].

The 2 forms of alexithymia, type 1 and type 2 [10], differ on the affective and cognitive dimensions [11]. Type 1 alexithymia includes high levels of both dimensions, whereas type 2 alexithymia only includes high levels of the cognitive dimension. Type 1 relates to reduced emotional reactivity (or a severe downregulation of emotional experience), and type 2 is typical emotional reactivity, but a reduced ability to interpret and describe that emotion [12].

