### Participants

We will recruit through local ASD support groups, online social media, and noticeboard advertisements (eg, at Federation University Australia). We will also use snowball recruiting to better penetrate the ASD community. Participants with an ASD (based on the assessments described in the Assessment section) will be assigned to the ASD group. Other participants will be assigned to the alexithymia-matched general population group (AM group).

The researchers will also use the 20-item Toronto Alexithymia Scale (TAS-20) total scores [40] to match the ASD group with the AM group without an ASD. Specifically, the number of participants in each group meeting criteria for alexithymia will be matched as indicated by TAS-20 scores ≥61, which is how groups have been matched in similar studies (eg, [32]).

The inclusion criterion is that participants are 18 years of age and older. The ASD group also has the added inclusion criterion of a confirmed ASD based on the assessment described in the Assessment section. Exclusion criteria include the participant having another mental health condition (other than an ASD if in the ASD group) diagnosed by a clinician and that the Kessler Psychological Distress Scale (K10) [41] indicates a significant level of distress (cut-off score of 22).

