### Comparator/Control Group

This study includes both a before-after, within-group comparator and a between-groups control group. To make the before-after comparison, participants will first partake in a baseline assessment task of emotion recognition before randomization to one of the experimental conditions. This baseline assessment task will be the same as the intervention task; however, participants will not be instructed to mimic the facial expressions prior to selecting an expression.

In addition to the before-after comparator, there will be a control condition. The control condition will also undergo the baseline assessment task; however, instead of participating in the mimicry intervention task, they will undergo a similar task with no mimicry element. This task will be identical to the instructed mimicry intervention task; however, instead of being instructed to mimic the facial expression, they will be instructed to “pay particular attention to the entire face prior to selecting an expression.” This instruction is aimed to match for attention levels.

A final point of comparison will be that participants will be first broken up into 2 groups, namely the AM group and ASD group. This comparison will provide the ability to analyze if any intervention effects only occur or are stronger in people with ASD, alexithymia, or the general population. The participant flow diagram can be seen in Figure 3.

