### Hypotheses

It is hypothesized that the condition that receives the mimicry task will show significantly better emotion recognition improvement scores (posttest minus baseline); the degree of alexithymia will negatively predict baseline scores; the degree of alexithymia will predict improvement scores (posttest minus baseline); when matched on alexithymia, the general population and ASD population will not significantly differ in emotion recognition improvement scores (posttest minus baseline); and when matched on alexithymia, the AM group and ASD group will not significantly differ on baseline emotion recognition scores.

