## Discussion

This paper describes, to our knowledge, the first study to assess an instructed mimicry task to increase emotion recognition ability in people with alexithymia and ASD. Despite the formulation of the alexithymia hypothesis, very few studies have assessed the impact of alexithymia in interventions aimed at increasing social functioning and in particular, emotion recognition. Additionally, to our knowledge, no other study has explored the benefits of instructed mimicry on emotion recognition in people with ASD and alexithymia. This mixed factor, 2x2x2, within-between design will assess the efficacy of the instructed mimicry task to increase FEER. This study design will enable the assessment of baseline and improvement scores individually for people with and without ASD while controlling for levels of alexithymia. This will allow analyses of how this intervention uniquely benefits ASD without the interference of alexithymia, which is known to frequently co-occur in ASD [9]. If this task is successful at increasing emotion recognition, it could provide easily accessible training to those with ASD, alexithymia, and other disorders that typically have high rates of alexithymia such as schizophrenia [59].

One proposed benefit of this intervention for people with alexithymia and ASD is that the software does not require supervision. This will likely benefit these populations as they typically enjoy computer-based interaction rather than social interaction, as indicated by previous studies (eg, [60]). This has the added benefit of improving access to the task as it could be used on a home computer, which may eliminate a key barrier to treatment.

Despite the benefits of this task and study design, some limitations are present. First, matching the ASD and AM groups on levels of alexithymia improves our ability to exclude alexithymia as a contributing factor of emotion recognition accuracy. Unfortunately, it also means that other confounding factors may have been systematically introduced when matching on alexithymia. This limitation will make it difficult to attribute any benefits of the intervention task specifically to autism. Additionally, when comparing emotion recognition accuracy, it will limit our ability to suggest whether emotion recognition difficulties are related to ASD or to alexithymia, as per the alexithymia hypothesis.

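### The AM group's result is framed as efficacy in the general population, but the group is selected to match the ASD group on alexithymia

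*Protocol article*

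**What the plan says.** All places are in the protocol article.

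- **Assessments** sets the target: "The main aim of the current study is to assess the efficacy of the intervention in the general population and an ASD population". The sentence goes on to ask whether highly alexithymic people benefit more. The section then says that the design needs a general-population group and an ASD group, matched on alexithymia.
- **Participants** defines the only group without ASD: "Other participants will be assigned to the alexithymia-matched general population group (AM group"). Its make-up is fixed by a matching rule: "the number of participants in each group meeting criteria for alexithymia will be matched as indicated by TAS-20 scores ≥61".
- **Assessments** shows that this make-up is built by selection: "participants will be prescreened online to facilitate creating this composition of participants".
- **Comparator/Control Group** says the two-group split will show "if any intervention effects only occur or are stronger in people with ASD, alexithymia, or the general population".
- **Hypotheses** expects that "the degree of alexithymia will predict improvement scores (posttest minus baseline"). It gives no direction.
- **Statistical Analyses** plans a mixed ANOVA (time, task, group) with IQ, depression and anxiety as covariates. It also plans a regression in four stages (Table 3): IQ, age and gender; autism; alexithymia; intervention. Table 3 lists no interaction.
- **Discussion** treats matching as a limitation because it may bring in confounders and hamper attribution to autism or alexithymia. It does not mention representativeness.

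**The concern.** A group whose share of alexithymic people is set by matching to an ASD group is not a sample of the general population in that respect. This would be harmless if alexithymia had no bearing on response. Here the trial expects improvement to depend on it, and asks whether intervention effects are stronger in alexithymic people.

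If the effect of mimicry does vary with alexithymia, the AM average is weighted towards whatever happens in alexithymic people. Reading it as general-population efficacy would answer part of the stated main aim for a different population. None of the stated analyses re-weights the estimate or shows how it changes with alexithymia.

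**Working it through.** **The plan's own figure.** Sample Size Calculation gives 58 evaluable participants for f² = 0.27, 5% significance and 80% power. A noncentral F test of overall R² with six predictors (IQ, age, gender, autism, alexithymia, intervention) returns N = 58, with power 0.808. The figure therefore reproduces with the six main effects of Table 3. It does not bear on which population the AM group represents. With a seventh predictor and the same f², the calculation needs 61, and power at 58 is 0.776.

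**Inputs for the point at issue.**

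- AM group: about 32 people, 16 per task (Table 2).
- Share q of the AM group with TAS-20 of 61 or more: by the matching rule and equal group sizes, equal to the ASD group's share. The document gives only a ceiling from a cited source: "Severe degrees of alexithymia are manifested in up to 65% of adults with ASD". I use 65% as the upper case and an assumed 40% as a lower one.
- Share p in the general population: not given. The nearest pointer is "alexithymia, which is known to frequently co-occur in ASD". I assume 5% to 20%.
- Mimicry-versus-control effect A in alexithymic people and B in others: not given, so assumed.

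**Head counts.**

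- AM group at 65%: 0.65 × 32 = 20.8 alexithymic, 11.2 not.
- AM group at 40%: 0.40 × 32 = 12.8 alexithymic.
- A representative 32: 0.05 × 32 = 1.6 to 0.20 × 32 = 6.4 alexithymic.

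**Effect.** The AM average is qA + (1 − q)B and the population average is pA + (1 − p)B. Their difference is (q − p)(A − B).

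| q | q − p for p = 5% | q − p for p = 20% |
|---|---|---|
| 65% | 0.60 | 0.45 |
| 40% | 0.35 | 0.20 |

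**Illustrations in percentage points of recognition.**

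- A = 10, B = 2, q = 65%: AM average 0.65 × 10 + 0.35 × 2 = 7.2. Population average 0.05 × 10 + 0.95 × 2 = 2.4, up to 0.20 × 10 + 0.80 × 2 = 3.6. The gap is 3.6 to 4.8.
- A = 10, B = 2, q = 40%: AM average 0.40 × 10 + 0.60 × 2 = 5.2. The gap is 1.6 to 2.8.
- A = 6, B = 4, q = 65%: AM average 0.65 × 6 + 0.35 × 4 = 5.3, against 4.1 to 4.4. The gap is 0.9 to 1.2.
- A = B: no gap, whatever the shares.

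If alexithymic people gained less (A below B), the gap would change sign.

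**The case against.** The other side has a good case, and much of it stands.

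- **The matching is disclosed.** The group's full name contains it, and the hypothesis that mentions the general population opens with the matching condition. That hypothesis needs no change. General population can also be read as shorthand for people without ASD, as in the closing summary of the Discussion.
- **The formal aims are worded more carefully.** Objective and Study Aims speak of adults with and without ASD and alexithymia. The efficacy hypothesis compares the two tasks over the whole sample. The loose wording is confined to Assessments and Comparator/Control Group, but Assessments calls it the main aim.
- **The direction of matching is not stated.** Participants does not say which group is adjusted. Choosing less alexithymic people with ASD would also satisfy the rule, and the ASD group would then be the less representative one. Given the 65% figure and the prescreening, raising the alexithymic share of the AM group is the more natural reading.

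A reader might infer three stronger points that the document does not support.

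- **That Comparator/Control Group promises a third arm that does not exist.** It describes two groups. Alexithymia cuts across both and enters the regression on its own, and lower scorers remain in the AM group unless every matched ASD participant is alexithymic.
- **That both groups are enriched for alexithymia.** Nothing selects for it in the ASD group. A high rate there would be its natural make-up.
- **That general-population benefit will be overstated two- to threefold.** That ratio (7.2 against 2.4 to 3.6) needs the 65% ceiling and invented effects. The trial's own rate is unknown, and it excludes other diagnosed conditions and high distress scores. Those exclusions are ordinary eligibility choices and no fault in themselves.

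**Conclusion.** The point holds as a limit on what the AM result may be said to show. The randomised comparison within the AM group is sound, and matching suits the ASD-versus-AM contrast. The AM average, however, estimates the effect in alexithymia-matched adults without ASD. It equals a general-population effect only if the two alexithymic shares agree or the effect does not vary with alexithymia.

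The size is (q − p)(A − B), and the document fixes none of these terms. Under the assumed shares the gap is 0.20 to 0.60 of the subgroup difference in effect. In points, it runs from about 1 (effects of 6 and 4) to nearly 5 (effects of 10 and 2) at the 65% ceiling. These figures are illustrations, not predictions.

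The hypothesis on alexithymia concerns improvement scores, which is not quite a statement that the task effect differs. The question in Assessments about extra benefit, and the similar one in Comparator/Control Group, show that such a difference is taken seriously. The conclusion is about an unsupported label and a missing estimate, not about bias in the trial's main randomised comparison.

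**What to change.** 1. In Assessments and Comparator/Control Group, restate the target as efficacy in *alexithymia-matched adults without ASD* instead of the general population.
2. In the Discussion limitations, add that the AM group's alexithymia distribution is set by matching, so its average effect need not carry over to the general population.
3. Add a task-by-TAS-20 interaction, with TAS-20 as a continuous score, to the Table 3 regression on improvement scores. A final fifth stage would leave Stages 1 to 4 as planned.
4. From that model report the mimicry-versus-control difference with its interval at a low score, for example 50, and at 61. The TAS-20 section counts 50 or less as no alexithymia and 51 to 60 as borderline, so a subgroup of 60 or less would mix two categories.
5. Rest any statement about non-alexithymic adults without ASD on the low-score estimate. Because the regression pools both groups, this assumes that the task effect at a given score is the same with and without ASD. State that assumption, or fit the model in the AM group alone.

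The cost is wording and one further model term from data already to be collected. As of June 2021 recruitment had not begun, so the change could be made before any data. The drawbacks are a narrower claim and a wide interval: the AM group has about 32 people, and randomisation is stratified by age and gender but not by alexithymia. The sample size was not set to detect an interaction, so the estimate and interval should be reported without leaning on its significance test.

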### Assessor Training and Supervision

The PPs will have pre-existing training in conducting clinical interviews, including mental status examination, as well as administration of symptom measures and cognitive testing. They will be supervised by approved supervisors and endorsed clinical psychologists with extensive clinical experience (at least 10 years) working with and diagnosing people who have an ASD. All psychologists will participate in the AMSE training [48], which entails working through the AMSE manual, examples, and posttests. The viewing, rating, and discussion of additional videos of adults with ASD will enhance interrater reliability and ensure understanding of diagnostic criteria.

Clinical interviews will be recorded, and AMSE scoring decisions will be made with one or, where it is difficult to reach consensus, both of the supervisors. Participants who meet AMSE criteria and have a confirmed historical diagnosis will be included in the ASD group.

### Measures

During the screening stage of the study, participants complete the K-10, TAS-20, AQ-10, and several single-item questions pertaining to demographic variables and known presence of other mental conditions. In the clinical interview with the PP, participants will be administered the DASS-21 and WASI-II, and the clinician will also use this time to complete the AMSE observational measure. Indication of context and time-point for each measure can be seen in Table 1.

**Table 1 table1:** Study design and measures.

Concept	Measure	Instrument	Condition/ time point				
			Online screening stage	Clinical interview stage	Experiment stage		
					Pretest	During Experimental task	Posttest
Primary outcome	FEER^a^ ability	FEER task Improvement score	-	-	X	X	-
Secondary Outcome	Acceptance / Enjoyment of task	Task satisfaction Questionnaire	-	-	-	-	X
Eligibility	Psychological distress	K-10^b^	X	-	-	-	-
	Depression and Anxiety	DASS-21^c^	-	X	-	-	-
	Predict ASD^d^ classification on the ADOS^e^	AMSE^f^	-	X	-	-	-
	Predict ASD classification	AQ-10^g^	X	-	-	-	-
	Alexithymia	TAS-20^h^	X	-	-	-	-
Control variables	Alexithymia	BVAQ^i^	-	-	X	-	-
	IQ	WASI-2^j^	-	X	-	-	-
	Demographics	Demographic information	X	-	-	-	-

^a^FEER: facial emotion expression recognition.

^b^K-10: Kessler Psychological Distress Scale.

^c^DASS-21: Depression Anxiety Stress Scales-21.

^d^ASD: autism spectrum disorder.

^e^ADOS: Autism Diagnostic Observation Schedule.

^f^AMSE: Autism Mental Status Exam.

^g^AQ-10: Autism Spectrum Quotient.

^h^TAS: Toronto Alexithymia Scale.

^i^BVAQ: Bermond–Vorst Alexithymia Questionnaire.

^j^WASI-2: Wechsler Abbreviated Scale of Intelligence.

#### K-10

The K-10 [41] is a measure of psychological distress. It consists of 10 items measured using 5 values that ask how often a specific feeling was felt over the past 4 weeks. Possible answers range from 1 “None of the time” to 5 “All of the time,” with higher values indicating more distress. Possible scores range from 10, indicating no distress, to 50, indicating severe distress. A cut-off score of 19 will be used to indicate the presence of case-level anxiety or depression [49]. The K-10 is a reliable and valid measure of psychological distress with high discriminant validity [41].

#### TAS-20

The 20-item TAS-20 [40] is the most widely used measure of alexithymia. It consists of 20 items, with each item being rated on a 5-point Likert scale between “strongly disagree” (1) and “strongly agree” (5). Higher scores designate higher degrees of alexithymia with a possible score ranging between 20 and 100. Cut-off scores have been developed with scores ≤50 suggesting no alexithymia, scores between 51 and 60 indicating borderline alexithymia, and scores ≥61 suggesting alexithymia [50]. The TAS-20 has been demonstrated to be a valid and reliable measure of alexithymia [40] with an internal consistency of α=.81 and test-retest reliability of .77 (*P*<.01).

#### Bermond–Vorst Alexithymia Questionnaire

The Bermond–Vorst Alexithymia Questionnaire (BVAQ) [11] is also a measure of alexithymia that aims to assess the alexithymia construct more comprehensively across 2 subdimensions, namely the cognitive and the affective. Measuring these 2 subdimensions aids in distinguishing between participants with type 1 and type 2 alexithymia. In total, there are 40 items rated on a 5-point Likert scale, with higher scores indicating higher levels of alexithymia. This model of alexithymia and the BVAQ have demonstrated strong validity and reliability [10,11].

#### DASS-21

The DASS-21 [46] is a self-report questionnaire that is designed to measure depression, anxiety, and stress/tension levels. Each of the 3 subscales contains 14 items that are scored on a 4-point Likert style scale, which ranges from 0, “did not apply to me at all,” to 3, “applied to me very much, or most of the time.” Total scores are calculated by summing the scores from the 3 subscales, with higher scores indicating more of that construct. The DASS has good convergent and divergent validity, with strong internal consistency and reliability, with Cronbach alphas observed at .94, .87, and .91 for depression, anxiety, and stress, respectively [51]. Additionally, the DASS has established normative data for adults with an ASD [52].

#### AMSE

The AMSE 2.2 [43] is an 8-item clinician observational assessment that aims to structure the documentation and observation of social, communicative, and behavioral function in people with ASD. The AMSE takes place during a clinical interview without adding extra work or time during the examination. Scores higher than 4 predict ADOS [53] classification with a sensitivity of 94% and specificity of 81% [44]. Interrater agreement is high at 0.97, and internal consistency was fair with a Cronbach α of .72 [43].

